### Methods: data collection, management, and analysis

#### Data collection and management

We will collect the participants’ characteristics (e.g., education) using patient surveys as standardized in German socio economic panels [45]. All outcomes will be collected with standardized patient surveys. All patient surveys will be performed by the same four interviewers based on an interviewer manual to ensure consistency.

Data will be collected using an electronic case report form (eCRF) and stored in an electronic data management system (REDCap) [46, 47]. The eCRF and data management system will be piloted with dummy participants (hypothetical patients). We will perform a sample of double data entry to prove data quality. Only authorized study personal will have access to the data management system.

To ensure high retention, the participants’ expenditure of time for study participation will be kept as low as possible. Moreover, due to the nature of the intervention, there will be no physical strain for the participants caused by study participation.

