#### Interventions

We include two groups of participants before (pre) and after (post) the introduction of the intervention. The group in the pre period (control group) will give informed consent based on standard consent forms from the Thieme-compliance publisher (https://shop.thieme-compliance.de/patientenaufklaerung/thieme/de/Artikel/Aufkl%C3%A4rungsb%C3%B6gen/c/00000), which represents routine care in the study center. The group in the post-period (intervention group) will give informed consent based on our newly developed evidence-based informed consent forms (see sub-study II). The change of the informed consent forms will be introduced at a pre-specified time-point. The informed consent procedures for surgery and for anesthesia will be performed together as far as feasible in the usual hospital workflow.

In addition, physicians performing informed consent in the post-phase will be offered a training in evidence-based decision-making to adequately implement the evidence-based informed consent forms. The training will be based on the basic curriculum for evidence-based decision-making, developed by the *German Network for Evidence-based Medicine*. A curriculum-based, blended learning training program for physicians and medical students has already been developed and pilot tested [37]. This training will be converted to an e-learning module to be independent of possible restriction due to the COVID-19 pandemic. In addition, e-learning with only short phases of virtual presence offers more flexibility. The training will also be adapted to address evidence-based decision-making on TKA. For major changes pilot testing will be considered.

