#### Blinding

Standard consent forms and evidence-based informed consent forms are obviously different. Therefore, blinding of medical staff will be impossible. We will not explicitly inform participants about receiving a “different” informed consent form but only about the nature of the study. The statistical analysis will be performed blinded.

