#### Outcomes and measurement instruments

We plan to measure the following patient-relevant outcomes:
Primary outcomes:Anxiety: subjective fear/anxiety of adverse events possibly caused by surgery or anesthesia
○ Measuring instrument: numeric rating scale 0–10 (validation see [38, 39]) and surgical fear questionnaire (SFQ) [40]. The SFQ comprises 8 items reflecting different aspects of surgery-related fear (e.g., anesthesia or side effects). All items are scored on a numeric rating scale 0–10. It is validated in adult patients scheduled for an elective surgery.○ Measure: meanNocebo-effect: patient reported adverse events (e.g., headache after anesthesia)
○ Measuring instrument: a questionnaire will be developed. We will use closed simple-choice questions (yes/no) to detect frequent adverse events and open-ended questions to detect other (less common) adverse events.○ Measure: proportion of patients with complications or adverse eventsSecondary outcomes:Knowledge or risk perception: questions for knowledge about benefits and risks
○ Measuring instrument: objective knowledge questions (e.g., correct risk assessment) derived in the development phase. The development will be based on previous experiences with the measure of informed choice [33, 34].○ Measure: proportion of correctly answered questionsSatisfaction with the physician-patient-communication and informed consent form
○ Measuring instrument: numeric rating scale 0–10 (validation see [41])○ Measure: meanQuality of life (QoL)
○ Measuring instrument: numeric rating scale 0–100 (validation see [42])○ Measure: meanPain and function
○ Measuring instrument: Oxford Knee Score (OKS) [43]. The OKS is a 12-item questionnaire with five scoring categories (validation see [43]).○ Measure: mean

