#### Recruitment

Based on the yearly caseload of patients with TKA in the study center, we anticipate a recruitment phase of 24 months. In the first 12 months participants receive the standard consent form (12 months pre-phase). After this period, the evidence-based consent form will be introduced and subsequent participants will receive the evidence-based consent form (12 months post-phase). Recruitment is expected to start in March 2021 and finish in February 2023. Study participants will be recruited by study nurses or physicians during the office hours of the clinic for orthopedics, trauma surgery, and sports traumatology of the Cologne-Merheim hospital. There will be no financial incentives for participation.

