In a second model, we will analyze the intervention effect on an individual level. This means, the study is analyzed as historical cohort study. In this model, the individual intervention components (informed consent forms, parallel performance of informed consent by orthopedic and aesthetic medical staff, participation on the training for evidence-based decision-making) are modelled as separate intervention components. We will perform this exploratory analysis to get insights into the isolated effect of evidence-based informed consent forms and interaction effects with other intervention components. We will adjust the models for baseline characteristics (age, sex, educational level, and marital status) and a potential time trend (since the comparison group is a historical control).

In case > 5% of data for an outcome are missing, we will impute the missing data by multiple imputation using the Markov chain Monte Carlo method. In addition to this primary analysis, we will perform a best-case/worst-case analysis to assess the robustness of results depending on missing data [48].

To quantify the statistical uncertainty, the associated 95% confidence intervals will be provided for all effect estimates. As we will conduct an explorative pilot study, we will not perform a test for statistically significant differences. We will prepare interrupted-time-series graphs to visualize the results [49].

All analyses will be performed using SAS software [50] and R [51].

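### The primary nocebo outcome rests partly on open-ended answers, and no masking to phase is stated for those who elicit or classify them

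*Protocol article*

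**What the plan says.** All of this is in the protocol article, sub-study III.

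- **Outcome.** Under Outcomes and measurement instruments, the nocebo effect is one of two primary outcomes. It is patient-reported and summarised as the proportion of patients with complications or adverse events. On the questionnaire, which is still to be developed: "We will use closed simple-choice questions (yes/no) to detect frequent adverse events and open-ended questions to detect other (less common) adverse events". Table 1 places it 3 days after discharge.
- **Who collects it.** Data collection and management states "All outcomes will be collected with standardized patient surveys" and then "All patient surveys will be performed by the same four interviewers based on an interviewer manual to ensure consistency".
- **How phase is set.** Recruitment gives 12 months on the standard form, followed by 12 months on the new one. Interventions adds: "The change of the informed consent forms will be introduced at a pre-specified time-point".
- **Who is blinded.** The Blinding section says of the visibly different forms: "Therefore, blinding of medical staff will be impossible". Participants are not told explicitly that their form is different, and the statistical analysis is to be blinded. Interviewers and coders of free text are not mentioned.
- **Models.** Statistical model describes a segmented regression in which β2 is the level change. It is to be adjusted for unforeseen time-varying confounders. For the exploratory individual-level model: "We will adjust the models for baseline characteristics (age, sex, educational level, and marital status) and a potential time trend".
- **Limitations.** Confounding, temporal effects and external validity are named. Assessor bias is not.

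**The concern.** With an any-event measure, one accepted free-text mention is enough to move a patient from no event to event. Two human steps lie behind that mention: how far the interviewer probes, and whether someone counts the answer as an adverse event. Nothing in the article says that either step is taken without knowledge of the phase, and the design makes the phase easy to infer.

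Blinding the analysis does not help, because it starts after the answers have been obtained and classified. There is also no concurrent control group. If assessors probe or classify differently once the new form is in use, the change coincides exactly with the intervention. The 95% confidence interval would not show it, since it reflects sampling error only.

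The pilot is meant to supply the basis for the sample size of a definitive trial (Sample size), and positive indications are to lead to that trial (Discussion and practical implications). A distorted nocebo estimate would carry into both.

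**Working it through.** **1. The plan's own figure.** 220 × 0.9 = 198 analysed, or 99 per phase. The probability of seeing a 2% problem at least once is 1 − 0.98^198 = 0.982, which agrees with the stated 98%. This point does not affect that figure.

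**2. Where a shared shift goes.** Write the plan's linear predictor as β0 + β1T + β2X + β3(T − T0)X, with X = 1 after the switch. Suppose all assessors change their recording by δ from the switch date. This adds δX, and the predictor becomes β0 + β1T + (β2 + δ)X + β3(T − T0)X. Only the sum β2 + δ can be estimated. Neither the trend terms nor patient covariates separate the two parts. A gradual, roughly linear drift would instead be partly absorbed by the slope terms. A step would not.

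**3. Possible size.** The document gives no event rates, so every rate here is an assumption.

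*Elicitation.* Let closed items flag a share c of patients, let the open question flag a further share q of the rest before the switch, and let the open yield fall by a fraction r afterwards. The false change is −(1 − c) × q × r.

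| c | q | r | False change |
|---|---|---|---|
| 0.6 | 0.1 | 0.25 | −0.010 |
| 0.4 | 0.2 | 0.50 | −0.040 × 1.5 = −0.060 |
| 0.2 | 0.2 | 0.50 | −0.080 |
| 0.2 | 0.3 | 0.50 | −0.120 |

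The third row in full: 0.8 × 0.2 × 0.50 = 0.080. The range is 1 to 12 points. If the open yield rose instead, the sign would reverse.

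*Classification.* If 10–30% of patients depend on an ambiguous open answer, and acceptance differs by 10–30 points between phases, the bias runs from 0.1 × 0.1 = 1 point to 0.3 × 0.3 = 9 points. At 20% and 20 points it is 4 points.

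**4. Yardstick.** For a simple pre/post difference with 99 per phase, SE = √(2p(1 − p)/99). This is 0.071 at p = 0.5, 0.065 at p = 0.7 and 0.057 at p = 0.8. It is not the standard error of β2 in the planned negative-binomial segmented model and serves only as a scale. In the monthly series there are about 99/12 = 8.25 patients a month, so one reclassified patient moves a monthly proportion by about 1/8.25 = 12 points.

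**5. What an interviewer term can do.** This was checked by simulation: 4,000 replicates, 99 per phase, assumed base proportion 0.50, interviewer offsets −0.10, −0.03, +0.03 and +0.10, no true effect.

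| Scenario | False effect without term | With term |
|---|---|---|
| Same interviewer mix in both phases | 0.001 | 0.001 |
| Mix moves from 10/20/30/40% to 40/30/20/10% | −0.065 | 0.001 |
| All four record 0.08 fewer events after the switch | −0.081 | −0.081 |

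The term corrects a changing mix. It leaves a shared shift untouched.

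**The case against.** The strongest reply is that this is silence in a condensed article. The questionnaire is still to be developed and the interviewer manual is not shown, so coding rules may exist there. That stands: a reader might infer that there is no masked coding, but the document supports only that none is stated. The gap is still worth closing, because the Blinding section sets out who is and is not blinded and leaves out the people closest to a primary outcome.

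The safeguards are also real. The same four people and one manual in both phases cancel stable interviewer differences while the mix stays balanced. Frequent events are taken by closed items, and the open questions cover only "open-ended questions to detect other (less common) adverse events". This narrows the route for bias but does not close it under an any-event measure.

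A reader might go further and say that the bias favours the new form. The document does not support that. Nowhere does it say that interviewers know the phase, classify the answers or prefer either form. Knowledge of the phase is an inference from the calendar, and over-elicitation after the switch would work against the new form.

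A reader might also see the missing interviewer term as the main flaw. It is not. The term helps only if the mix changes, which nothing in the document suggests, and the model in which patient-level covariates are listed is exploratory. For the primary hospital-level analysis, the promised adjustment for time-varying confounders could cover a change of mix. Nor is there a basis for saying that the anxiety or satisfaction means are biased: these are patients' own answers on numeric scales.

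Finally, this is a pilot without significance tests. That lowers the stakes, since no confirmatory claim is at risk, but the estimate still feeds the planning of the next trial.

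**Conclusion.** The point holds as a limited risk that is cheap to reduce. The article fixes an any-event primary outcome that can turn on one open-ended answer, a phase that can be read from the date, and no concurrent control. It states no masking for those who elicit or classify the answers. A step shared by phase-aware assessors would be indistinguishable from the level change β2, and could go in either direction.

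Its size cannot be derived from the document. The illustrations give 1 to 12 points for elicitation and 1 to 9 for classification, against about 6 to 7 points of sampling error in a simple comparison. The bias could therefore be negligible or exceed the standard error. The conclusion rests on one inference, that interviewers can tell the phase from the date. It does not show that bias will occur.

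**What to change.** 1. Record open-ended answers verbatim. After data collection, have an existing team member who did not interview those patients code each answer as event or no event, in random order, with dates, phase and form hidden.
2. Build the primary nocebo variable from the closed items plus these masked codes.
3. Report a closed-items-only version as a sensitivity analysis. Masked coding removes classification bias but cannot recover answers that were never probed for.
4. State in the Blinding section whether interviewers and coders are masked to phase, and add assessor bias to the Limitations.
5. Optional and secondary: store an interviewer ID in the eCRF, show interviewer shares by phase, and add interviewer (3 degrees of freedom for four people) to the exploratory individual-level model as a sensitivity check against a changing mix only.

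The cost is one masked export and a small amount of coding by existing staff, plus one eCRF field if item 5 is adopted. Sample size, schedule and primary model stay as they are.

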#### Statistical model

We will report baseline characteristics of the study population and outcomes descriptively.

We will use an ITS analysis to determine level and slope changes after the implementation of the evidence-based informed consent forms. We will use segmented regression models for our analysis. The basic model is *Y*_*t*_ = *β*_0_ + *β*_1_*T*_*t*_ + *β*_2_*X*_*t*_ + *β*_3_(*T* − *T*_0_)*X*_*t*_

*X*_t_ is a dummy which differentiates pre- and post-intervention periods. *T* is the time since the start of the study in months. β_0_ is the base level. β_1_ is the course of the slope before the implementation of the intervention. β_2_ is the level change, which describes the immediate effect on *Y* after the implementation of intervention *X*. β_3_ is the course of the slope after the implementation of the intervention, whereby *T*_o_ is the time of beginning of the study. We will use negative-binomial regression models for all count data (nocebo effect and objective knowledge questions) and generalized linear model for outcomes which can be analyzed as continuous variables (anxiety, satisfaction, quality of life, OKS).

We will create two models. One model will analyze the intervention as a complex package of measures on hospital level. The intervention effect will be analyzed on the hospital level. We will adjust the analysis for potential unforeseen time-varying confounders (e.g., changes of the standard consent form by hospital information policies, structural changes in consent because of corona pandemic). Potential confounders for each outcome will be identified based on visual inspection of trajectory curve and content-related thinking. We will assess autocorrelation by examining the plot of residuals.

In a second model, we will analyze the intervention effect on an individual level. This means, the study is analyzed as historical cohort study. In this model, the individual intervention components (informed consent forms, parallel performance of informed consent by orthopedic and aesthetic medical staff, participation on the training for evidence-based decision-making) are modelled as separate intervention components. We will perform this exploratory analysis to get insights into the isolated effect of evidence-based informed consent forms and interaction effects with other intervention components. We will adjust the models for baseline characteristics (age, sex, educational level, and marital status) and a potential time trend (since the comparison group is a historical control).

In case > 5% of data for an outcome are missing, we will impute the missing data by multiple imputation using the Markov chain Monte Carlo method. In addition to this primary analysis, we will perform a best-case/worst-case analysis to assess the robustness of results depending on missing data [48].

To quantify the statistical uncertainty, the associated 95% confidence intervals will be provided for all effect estimates. As we will conduct an explorative pilot study, we will not perform a test for statistically significant differences. We will prepare interrupted-time-series graphs to visualize the results [49].

All analyses will be performed using SAS software [50] and R [51].

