## Feasibility/piloting

### Sub-study III: monocentric interrupted time series (ITS) pilot study

We will conduct a monocentric pilot study. This pilot study will be performed following a pragmatic trial approach to increase applicability to the German context of informed consent procedures [35]. Our primary analysis is an ITS analysis approach. Using an ITS analysis, will allow us to compare the outcome trend (level and/or slope changes) before and after the introduction of the newly developed evidence-based informed consent forms [36].

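### The segmented model sets T0 at study start, so β2 is not the level change at the switch of forms; separately, β3 is labelled the post-phase slope but is the change in slope

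*Protocol article*

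**What the plan says.** Under Sub-study III the protocol article states: "Our primary analysis is an ITS analysis approach". The Statistical model section gives its purpose: "We will use an ITS analysis to determine level and slope changes after the implementation of the evidence-based informed consent forms". The printed model is

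Y = β0 + β1·T + β2·X + β3·(T − T0)·X,

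where X is 0 before and 1 after the intervention. The terms are defined as follows:

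- T "is the time since the start of the study in months".
- β1 is the slope before implementation.
- β2 "is the level change, which describes the immediate effect on" Y once the intervention is in place.
- β3 "is the course of the slope after the implementation of the intervention, whereby" T0 "is the time of beginning of the study".

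The Recruitment section places the switch after a 12-month pre-phase, followed by a 12-month post-phase. The section on missing data and reporting promises 95% confidence intervals for all effect estimates and no significance tests. No other part of the article gives a different meaning for T0 or β3.

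**The concern.** Two definitions do not fit the equation they describe.

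First, if T starts at 0 when the study starts and T0 is also study start, the last term is T·X. β2 then describes month 0, a year before any patient receives a new form. That conflicts with its stated meaning as the immediate effect of the change.

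Second, the pre-phase trend β1·T is not switched off when X becomes 1. β3 is what is added to that trend, not the post-phase trend itself.

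These are the two coefficients that the primary analysis exists to estimate. Since there is no significance testing, the estimates and their intervals are the result. The article also says that a definitive cluster-randomised trial is planned if the pilot indicates positive effects, so a misread sign or size could carry into that decision.

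**Working it through.** The plan states no figure for these coefficients. Its one sample-size figure, 98%, reproduces as 1 − 0.98^198 = 0.9817 and has no bearing on this point.

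**Inputs.** From the Statistical model section: the equation, T in months from study start, and T0 = study start, hence T0 = 0. From Recruitment: switch at about T = 12, with 12 months on each side. The level and slope changes below are assumptions, since the protocol gives none.

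**What β2 measures.** Let L be the level change at the switch and D the change in slope.

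- Pre-phase line: β0 + β1·T.
- Post-phase line with T0 = 0: (β0 + β2) + (β1 + β3)·T.
- Gap between the lines at month T: β2 + β3·T.
- At the switch, L = β2 + 12·β3, and D = β3. Hence β2 = L − 12·D.

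β2 equals L only if D = 0.

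| Assumed L | Assumed D per month | β2 with T0 = 0 (as written) | β2 with T0 = 12 |
|---|---|---|---|
| −1 | 0 | −1.0 | −1.0 |
| −1 | −0.05 | −1 + 0.6 = −0.4 | −1.0 |
| −1 | −0.10 | −1 + 1.2 = +0.2 | −1.0 |
| −1 | +0.10 | −1 − 1.2 = −2.2 | −1.0 |
| 0 | −0.10 | 0 + 1.2 = +1.2 | 0 |

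Noise-free least-squares fits to 24 monthly points return the same values. The sign reverses when D has the same sign as L and exceeds |L|/12 in size, which is 1/12 = 0.083 per month for L = −1.

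**What β3 measures.** From the two lines, the post-phase slope is β1 + β3 for any choice of T0. With an assumed pre-phase slope of +0.05 and D = −0.10, the fit gives β3 = −0.10 while the post-phase slope is +0.05 − 0.10 = −0.05. The label is correct only if β1 = 0.

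**Precision.** Assume 24 equally weighted, independent monthly points, T = 1 to 24, with residual SD 1. Each 12-month segment has a sum of squares of T about its mean of 143, with means 6.5 and 18.5. The variance of the gap at month c is

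1/12 + (c − 6.5)²/143 + 1/12 + (c − 18.5)²/143.

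- c = 0: 0.379 + 2.477 = 2.855, SE = 1.69. This is β2 as written.
- c = 12: 0.295 + 0.379 = 0.674, SE = 0.82. This is β2 with T0 = 12, and equally β2 + 12·β3 with T0 = 0.

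The two codings give the same fitted values. Only the coefficient carrying the β2 label differs.

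**The case against.** The strongest reply is that these are wording slips, not a wrong model. The equation is the usual segmented form, and subtracting T0 would be pointless if T0 were 0. The surrounding text makes clear that changes at implementation are wanted. The fit and the promised time-series graphs are the same under either coding, the level change can be recovered exactly, and the study is an exploratory pilot without tests.

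Most of that stands and limits the consequence. It does not remove the point. The article itself fixes T0 in words, and nothing tells the analyst or reader to compute β2 + 12·β3. Reading T0 as a slip also leaves the β3 label wrong. An analysis plan that is not shown may define the terms correctly, but it would then contradict the article.

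A reader might go further in three ways that the documents do not support.

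- **That the analysis loses precision.** The standard errors 1.69 and 0.82 (ratio 2.06) belong to different quantities. The SE of the level change at the switch is 0.82 under both codings.
- **That the sign will be reversed.** This needs a slope change that the protocol does not state. With none, β2 is correct.
- **That patients near the switch are miscoded, because enrolment precedes the TKA consent form by some weeks.** The article does not index X by enrolment month. Interventions says "The change of the informed consent forms will be introduced at a pre-specified time-point". Recruitment says "After this period, the evidence-based consent form will be introduced and subsequent participants will receive the evidence-based consent form". These are compatible. Interventions and Participant timeline define phase by the form received, and Table 1 has a separate interruption column. The process evaluation records whether the new form was used. Any attenuation figure would require assuming that all month-12 enrolees are miscoded.

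**Conclusion.** The point holds as an error of definition in the primary analysis. As written, β2 and its 95% interval describe the pre/post gap at month 0, and β3 is described as a slope when it is a difference of slopes. The two errors are independent: only the T0 definition affects β2, and only the label affects the reading of β3.

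The error in β2 is 12 times the slope change: nothing if the slope change is zero, and 1.2 points for an assumed 0.10 per month, enough to turn −1.0 into +0.2. The factor 12 rests on a switch at month 12. If the interruption shown in Table 1 moves the switch, the factor becomes that month. For the negative-binomial outcomes the same algebra applies on the link scale, assuming a log link. The harm is a misread coefficient. The model fit, the graphs, the attainable precision and the sample size are unaffected.

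**What to change.** In the Statistical model section, define T0 as the time at which the new consent forms are introduced, about month 12 on the stated time scale. State that β2 is the level change at T0, β3 is the change in slope, and β1 + β3 is the post-phase slope. If the T0 = 0 coding is kept for any reason, report β2 + 12·β3 with its 95% confidence interval as the level change, not β2.

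The cost is a few words in the model definition and one line of analysis code. No patients, visits or data items change.

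### The primary nocebo outcome and the knowledge outcome are defined as proportions but assigned a negative-binomial count model; for nocebo as defined, this gives intervals that are too wide when events are common

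*Protocol article*

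**What the plan says.** All references are to the protocol article, sub-study III.

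- **Outcomes and measurement instruments, nocebo effect (primary).** The questionnaire uses "closed simple-choice questions (yes/no) to detect frequent adverse events" and adds open-ended questions for less common events. The summary measure is the "proportion of patients with complications or adverse" events.
- **Outcomes and measurement instruments, knowledge (secondary).** "Measure: proportion of correctly answered" questions.
- **Statistical model, distribution.** "We will use negative-binomial regression models for all count data (nocebo effect and objective knowledge questions"). All other outcomes get a "generalized linear model for outcomes which can be analyzed as continuous variables (anxiety, satisfaction, quality of life, OKS"). A generalized linear model could be binomial, but here the term is reserved for the continuous outcomes.
- **Statistical model, two levels.** The first model is a segmented regression in monthly time at hospital level. Then: "In a second model, we will analyze the intervention effect on an individual level". No other distribution is named for that second model.
- **Statistical model, inference.** No significance tests are planned, and "the associated 95% confidence intervals will be provided for all effect estimates".

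**The concern.** A patient either has an adverse event or does not, and a knowledge score cannot exceed the number of questions. Both measures are bounded and, before any clustering of answers, have binomial variance. The negative binomial is meant for unbounded counts that vary more than Poisson counts. The article therefore names a model that does not belong to the measure it names, and for nocebo this affects a primary outcome.

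Because no tests are done, the effect estimates and their 95% intervals are the only inferential output. The Sample size section says that the pilot is meant to supply the data basis for planning a definitive trial. An interval that overstates the uncertainty, or an estimate of something other than the stated proportion, would be carried into that planning.

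**Working it through.** **The plan's own figure.** 220 × 0.9 = 198 analysed, and 1 − 0.98^198 = 0.982, which matches the stated 98%. This calculation does not involve the outcome model, so nothing below changes the sample size.

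**Inputs.** From the article: 198 analysed, so 99 per phase (110 × 0.9), and 24 monthly points. Not in the article, so assumed over a range: the nocebo proportion p, the number of knowledge items K, the proportion correct q, and the within-patient correlation of answers ρ.

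**Nocebo, yes/no per patient.** The true variance is p(1 − p). The negative-binomial variance is μ + αμ² with α ≥ 0, so at μ = p it is at least p. The best-fitting α is then about 0, which is the Poisson model. For a log ratio of two proportions with n per phase:

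- Poisson limit: SE = sqrt(2/(np))
- Binomial: SE = sqrt(2(1 − p)/(np))
- Ratio: 1/sqrt(1 − p)

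| Assumed p | Interval too wide by |
|---|---|
| 0.05 | 1.03 |
| 0.1 | 1.05 |
| 0.3 | 1.20 |
| 0.5 | 1.41 |
| 0.7 | 1.83 |

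With n = 99 per phase and an observed ratio of 1:

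- p = 0.5: the SEs are sqrt(2/49.5) = 0.201 and sqrt(1/49.5) = 0.142. The 95% intervals are 0.67 to 1.48 (Poisson limit) and 0.76 to 1.32 (binomial).
- p = 0.1: the SEs are sqrt(2/9.9) = 0.449 and sqrt(1.8/9.9) = 0.426. The intervals are 0.41 to 2.41 and 0.43 to 2.31, which is hardly a difference.

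**Check by simulation under no effect.**

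- Patient level, 99 versus 99, Poisson limit, 1000 runs: coverage of the nominal 95% interval was 0.97, 0.97, 0.995 and 0.999 at p = 0.1, 0.3, 0.5 and 0.7.
- Monthly segmented model, 198 patients over 24 months, log number of patients as offset, about 400 runs each: the dispersion was estimated as 0 in 85% to 100% of runs. Coverage for the level change was 0.98, 0.98, 1.00 and 1.00 at the same p. At p = 0.5 the median SE was 0.41, against an empirical SD of 0.28.
- A binomial-logit segmented model on the same data covered 0.95 to 0.97.

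**Knowledge, K items.** The variance-to-mean ratio of the score is (1 − q)(1 + (K − 1)ρ). It reaches the Poisson value of 1 at ρ = [q/(1 − q)]/(K − 1). For K = 10 this is 1/9 = 0.11 at q = 0.5, 2.33/9 = 0.26 at q = 0.7 and 4/9 = 0.44 at q = 0.8. Below these correlations the intervals are too wide; above them the excess disappears. At q = 0.6 and K = 10, the factor is 1/sqrt(0.4) = 1.58 with ρ = 0 and 1/sqrt(0.4 × 1.9) = 1.15 with ρ = 0.1.

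**Denominator.** If the monthly number of patients with events were modelled without a denominator, the expected count would be (patients that month) × p and would move with recruitment. With an assumed 120 patients before and 78 after, and constant p, the expected ratio is 78/120 = 0.65 with no true effect. A simple before/after count model without trend terms gave a median ratio of 0.66 in simulation, with coverage of 0.68 at p = 0.3 and 0.45 at p = 0.5. This shows only what the denominator protects against.

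**The case against.** The strongest reply is that the authors may mean the number of adverse events per patient. The questionnaire has several yes/no items plus open questions, and the text says count data. A negative binomial would then be reasonable. That stands as a possible intention, but it moves the error rather than removing it, because the summary measure would then be misstated in the outcomes section. One of the two places has to change.

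It can also be said that this is an explorative pilot, that outcomes are also reported descriptively so that raw proportions stay available for planning, and that any excess width is on the cautious side. All of this is true, and it limits the importance of the point.

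Three stronger readings are tempting, and the article does not support them:

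- *That the confidence intervals are simply wrong.* With a patient denominator the nocebo error runs in one direction and almost vanishes at low p. For knowledge it may not arise at all.
- *That a fall in caseload will appear as a false fall in nocebo effects.* The article gives only a basic model and does not say what the monthly response is for each outcome. An offset is a detail often left to the analysis plan, and silence about it is not a plan to omit it. Any size attached to such an effect rests on an invented recruitment pattern.
- *That the imputation has the same fault.* The text says "we will impute the missing data by multiple imputation using the Markov chain Monte Carlo method". It does not state a multivariate-normal form, so implausible values for yes/no data cannot be inferred from it.

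**Conclusion.** The mismatch is real and lies in what the article states, not in what it leaves out: two outcomes, one of them primary, are defined as proportions and assigned a count model.

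For nocebo as defined, the result is intervals too wide by 1/sqrt(1 − p): about 3% to 5% at p of 0.05 to 0.1, 20% at 0.3, 41% at 0.5 and 83% at 0.7. All of these proportions are assumptions. A common outcome is possible, since it is any event and the closed questions target frequent ones, but the article gives no figure. For knowledge the direction is known only below a certain within-patient correlation, and no size can be fixed. The influence of recruitment is conditional on a missing denominator.

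This should be corrected before analysis. It does not threaten the pilot: there are no tests, so no false claim of significance arises, and the sample size stands.

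**What to change.** Reconcile the two sections in one of two ways.

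1. **Keep the proportions.** For nocebo, use binomial (logistic) segmented regression with patients with an event out of patients assessed each month, and logistic regression in the individual-level model. For knowledge, use quasi-binomial or beta-binomial regression of correct answers out of items, which allows for correlated answers within a patient.
2. **Redefine nocebo as a count.** State the measure as the number of adverse events per patient, keep the negative binomial, and use the log of the number of patients as an offset in the monthly model. Knowledge still needs a bounded model as in option 1.

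In both cases, state the monthly response and its denominator. The cost is wording in the plan and analysis code; data collection, conduct and sample size do not change.
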